## Methods/design

The VCPS evaluation will employ a stepped wedge cluster randomised trial design, where the intervention is sequentially implemented at eight facilities. The ‘steps’ are the order in which these sites cross-over from the control condition (pre-VCPS) to the intervention condition (VCPS). The sequence of the steps is randomised, allowing for control of potential confounding temporal trends. The cross-over will occur across 8 waves or steps (one site per step), each 1 month apart with a 2 month ‘in-transition’ period (see Fig. 1).

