**Fig. 1 Fig1:**
[figure not shown]
VCPS stepped wedge cluster randomised control trial design. There are a total of 8 steps, with each step being one month apart. The light blue represent sites unexposed to the intervention (control). White represents sites where the service is being introduced and no data will be used in the analysis. Dark blue represents sites exposed to the VCPS, and purple the service continuation and evaluation

The virtual pharmacy service will be delivered in six rural NSW hospitals that do not have an on-site pharmacist but are using electronic medication management and patient record systems and have more than twenty inpatient admissions per month; and two remote hospitals that have between seven and thirteen admissions per month and fit the other inclusion criteria. All adult patients of emergency departments and inpatient wards of the participating hospitals will be included in the study. The order of the site implementation will be determined by computer-generated random numbers.

The intervention will consist of utilising the eMR, eMeds and a wireless teleconferencing cart with two–way audio and visual called a ‘Wallie’ to provide clinical pharmacy services to study sites. Virtual Pharmacists will work 8.30 am to 4.30 pm, Monday-Friday of each week over the study period where it is anticipated they will see up to ten patients per pharmacist per day.

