Economic analysis (cost effectiveness) & scalability	HIU reports	Facility
**Process Measure**	**Data Source**	**Level of Data**
Number of medication reconciliation completed	eMR report EM002	Facility
Number of medication lists on discharge	Custom eMR report	Patient
Number of referrals/ number of referrals completed	eMR report PC011	Patient
Pharmacist Interventions	eMR DA2 Clinical Pharmacy Interventions	Patient
Time taken to undertake interventions	eMR DA2 Clinical Pharmacy Interventions	Patient
Time taken to provide education	eMR DA2 Clinical Pharmacy Interventions	Patient
Number of consultations	eMR report PC011	Patient
Uptake of pharmacy recommendations	eMR DA2 Clinical Pharmacy Interventions	Patient
Number of pharmacist AMS reviews	eMR report PC011/ eMR Report EM008	Patient

The primary outcome variables are: 1) the proportion of separations (“discharged home by the hospital”) where the medication reconciliation occurred on admission; and 2) the proportion of separations (“discharged home by the hospital”) where the medication reconciliation occurred on discharge. Secondary outcome variables include 28-day readmission, hospital length of stay (LOS), number of falls and detection of medication-related errors. Our analyses will comprise generalised linear mixed models, with fixed effects for time, period (pre vs post), and patient-level confounding variables, as well as random effects for facility and patient to model clustering/repeat measures. Analyses will exclude separations where the patient is transferred to another facility.

Sample size: Across the eight sites a referral rate of 29 patients per month is estimated yielding approximately 2088 patients over the intervention period. Assuming a baseline medication reconciliation rate on admission of 11% (a similar rate for discharge medication reconciliations), an intra-class correlation of 0.05, and an average of 29 patient separations per site per month,) there will be over 90% power to detect an absolute 10% increase in the proportion of reconciliations performed on admission and discharge, with a type 1 error rate of 2.5%.

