A staff focus group will be held at each participating site 3 months after the beginning of the VCPS transition period. The focus group will investigate the perceived acceptability of the service for staff. All staff who work in clinical areas where the VCPS operates will be asked to participate in the focus group. Senior staff and managers’ will participate in a separate focus group to all other staff to take into account potential power relationships that may inhibit the responses of junior staff. The focus group will be held 3 months after the VCPS commences to provide adequate time for staff to be exposed to the service. The focus group discussion will explore the issues, benefits, barriers and overall acceptability of the VCPS. A participation consent form is available from the corresponding author.

A qualitative approach will be used to undertake focus groups with participating staff (*n* = 25). The focus groups will investigate implementation processes and those affected by them to understand the context of VCPS implementation [29, 30]. The focus groups will be audio-recorded, transcribed verbatim and entered into QSR NVivo. Thematic analysis will be utilised to deductively and inductively identify barriers and facilitators to the VCPS implementation. Data files and transcripts will be stored on a password protected server only accessible by the research team.

There was no patient or public involvement in the research design. Community consultation with Australian Indigenous communities in the study sites will be conducted prior to the VCPS implementation to explain the project and identify and respond to any concerns. Indigenous Australian comprise up to 60 % of the population in some sites. If community Elders do not support the pharmacy service, or the study, Indigenous people will not be included in the data collection. Indigenous research team members will conduct the consultations.

Data monitoring committee: A data monitoring committee has not been formed because there are minimal risks associated with the study. However, a project governance group has been formed that includes academic and research pharmacists, government clinical practice and telehealth specialists and local health executives. This group will meet quarterly and will be responsible for monitoring the project progress and addressing any problems that arise.

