We also acknowledge the limitations of this trial, including: variability of sites, staffing and patient populations and self-report measures of medication adherence. First, participating sites are all small rural or remote hospitals with varying numbers and skill sets of staff. While technology has been well integrated into healthcare across the region, staff may not be familiar with how to use it or there could be system failures that prevent the pharmacy service delivery.

The identified limitations highlight the challenges of running an RCT of this kind under real-world conditions (e.g. casual staff, working with a diverse population, etc.). Despite these potential limitations, this trial is one of the most methodologically rigorous trials of virtual pharmacy interventions that exists to date. We will make extensive efforts to control for any sources of potential bias, imprecision, or multiplicity of analyses. Should modifications to the protocol be required these will be updated in the ANZCTR record as soon as they occur (Appendix).

This paper describes the protocol for a stepped wedge clustered randomized controlled trial designed to evaluate the effectiveness of a virtual pharmacy service delivered in eight rural or remote hospital sites. We aim to demonstrate the effectiveness of pharmacy interventions for rural populations, and inform best practise for using virtual healthcare to improve access to pharmacy services.

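### The single pre/post term is not an average effect if the VCPS effect keeps changing after the excluded transition; add a prespecified month-by-month service-time model beside it

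*Protocol article*

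**What the plan says.** The analysis paragraph of Methods/design specifies the model: "Our analyses will comprise generalised linear mixed models, with fixed effects for time, period (pre vs post), and patient-level confounding variables". Facility and patient enter it as random effects. The only treatment term is the pre/post indicator. No term in the article lets the effect depend on how long a site has had the service.

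The layout is given earlier in the same section: "The cross-over will occur across 8 waves or steps (one site per step), each 1 month apart". Each site also has a two-month transition. The legend to Fig. 1 explains how those months are handled: "White represents sites where the service is being introduced and no data will be used in the analysis". So each site contributes control months, then a two-month gap, then service months.

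Two other places bear on whether the service might change over time. The limitations in the Discussion say that "staff may not be familiar with how to use it or there could be system failures that prevent the pharmacy service delivery". The paragraph on data monitoring says of the governance group: "This group will meet quarterly and will be responsible for monitoring the project progress and addressing any problems that arise".

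**The concern.** In a stepped wedge trial the treatment effect is estimated largely by comparing sites that have crossed over with sites that have not, within the same month. Late in the roll-out, sites that have had the service for a while also act as comparators for sites that have just started. If the effect is the same in every service month, this does no harm. If it grows or fades with months of service, the later service months partly serve as controls and enter the single coefficient with negative weight.

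The test of no effect is not in question. What is at stake is the size of the reported effect. A service that improved with use would look weaker than it was, and one that faded would look stronger. The secondary outcomes use the same models. The cost-effectiveness and cost-benefit analyses rest on changes in readmission, length of stay and adverse events. The article does not say which model supplies those inputs, but the single-term estimate would be a natural choice.

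**Working it through.** **Inputs from the protocol article (Methods/design).** Eight sites, one site per one-month step, a two-month transition excluded at each site, 29 separations per site per month, ICC 0.05, baseline 11%, target increase 10 points (so 21%), type 1 error 2.5%, total 2088.

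**Assumptions.** Fig. 1 is not shown, so the numbers of control months before the first step and of exposed months at the last site are assumed to be one each. This gives 1 + 7 + 2 + 1 = 11 calendar months, with 36 control and 36 service site-months. Service months 1 to 8 are seen at 8, 7, 6, 5, 4, 3, 2 and 1 sites. The 2.5% is taken as two-sided. The repeat-patient random effect is ignored.

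**The plan's figures.** 72 site-months × 29 = 2088, the stated total. The stated power of over 90% is reproduced by an eight-step wedge of nine months without a gap: pooled variance 0.16 × 0.84, SE 0.0268, power Φ(0.10/0.0268 − 2.241) ≈ 0.93. With the two-month gap and the same 72 site-months, power is about 73%. That is a separate matter and is not pursued here.

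**Method.** Generalised least squares on site-month means, with categorical months, a site random intercept and variance (0.11 × 0.89 + 0.21 × 0.79)/2 = 0.132. The pre/post estimate is a fixed linear combination of the site-month means. Adding its coefficients over sites for each service month gives the weight on that month's effect.

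| Service month after transition | 1 | 2 | 3 | 4 | 5 | 6 | 7 | 8 |
|---|---|---|---|---|---|---|---|---|
| Weight | 0.724 | 0.432 | 0.203 | 0.034 | −0.076 | −0.125 | −0.116 | −0.075 |

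The weights sum to 1 (within rounding) and the SE is 0.0346, or 3.5 points. A constant effect of 10 points returns exactly 10.

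**Assumed effect curves, in percentage points.** Expected estimate = Σ weight × effect.

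- 5, 10, then 15: months 3 to 8 together weigh 1 − 0.724 − 0.432 = −0.156, so 5 × 0.724 + 10 × 0.432 − 15 × 0.156 = 5.6. Average over equal months: (5 + 10 + 6 × 15)/8 = 13.1. By site-months: (8 × 5 + 7 × 10 + 21 × 15)/36 = 11.8.
- Linear growth from 5 to 20 (15/7 per month): Σ weight × (month − 1) = −1.21, so 5 − 1.21 × 15/7 = 2.4. Averages: 12.5 or 10.0.
- Linear decline from 20 to 5: 20 + 1.21 × 15/7 = 22.6. Averages: 12.5 or 15.0.
- Mild growth 8, 10, then 12: 8 × 0.724 + 10 × 0.432 − 12 × 0.156 = 8.2. Averages: 11.2 (90/8 = 11.25) or 10.7.

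Power under the first two curves is Φ(0.056/0.0346 − 2.241) ≈ 27% and about 6%.

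**Sensitivity.** Late service months carried negative weight in all 18 combinations of 1, 2 or 3 baseline months, 1, 3 or 6 final exposed months, and categorical or linear time. The same holds in the base layout for ICC 0.01 to 0.10. The month at which the sign changes moves with the layout: month 5 in the base case, month 7 with six final exposed months. Simulated logistic fits gave 6.2 and 2.5 points for the first two curves, so the pattern does not come from the linear scale.

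**Model with a separate effect per service month.** It is estimable in this layout and recovers the true average under every curve above. The SE of the average is 5.5 points with equal months and 4.7 points weighted by site-months.

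**Pooled alternative (month 1, month 2, month 3 or later).** The pooled term has SE 4.8 points. It recovers the truth only where the effect is flat from month 3. Under linear growth it gives 8.0 against a true month 3 to 8 mean of 14.6; under linear decline, 17.0 against 10.4.

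**The case against.** The strongest case against the point is that the design already deals with bedding-in. Two months at each site are dropped, and any build-up completed in that time causes no bias. This stands, and it limits the concern to change after the transition.

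Nor does the article show that such change will occur. The primary outcomes are tasks the virtual pharmacist carries out, so slow growth over many months is not the obvious expectation. The Discussion passage concerns differences in staff skills and possible system failures, not months of service. Quarterly governance review, and a pharmacist team spread over more live sites as roll-out proceeds, would act mainly in calendar time, which service-time terms do not model. All of this stands, so these passages make a varying effect conceivable and no more.

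The size of the gap also depends on the comparator. Weighting by site-months instead of equal months narrows it in all four curves, although it stays large for the first three.

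Finally, an analysis plan or full protocol may already hold a service-time sensitivity analysis, and its absence from the article is no fault. But the point rests on the model the article does state and on how its single coefficient may be read.

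A reader might infer that the planned estimate is wrong, or that the single term should be replaced as the main analysis. The documents support neither. The model is a standard one and correct under a constant effect, and replacing it would cost much precision.

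**Conclusion.** The point holds conditionally. The single pre/post term gives a valid test of no effect and an unbiased estimate if the effect is constant after the transition. If the effect continues to build or fade, the coefficient is not an average of the monthly effects. In the assumed base layout it weights the first two service months at 0.72 and 0.43, and months 5 to 8 together at about −0.39. The error could be several points or more: 5.6 against 13.1 or 11.8, and 2.4 against 12.5 or 10.0, under two assumed growth curves.

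The negative late weights held in every layout tried; the month at which they begin did not, and depends on the figure that is not shown. The curves are illustrations, not predictions. This is a worthwhile low-cost improvement, not a defect that invalidates the primary analysis.

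**What to change.** Keep the single-term model as the primary test and estimate. In the analysis paragraph of Methods/design, or in the statistical analysis plan, prespecify beside it:

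- the same model with the pre/post term replaced by a separate effect for each service month after the transition;
- a report of the monthly effects and their average, with the weighting stated in advance (equal months or site-months);
- a rule that, if the two models disagree materially, the single coefficient is not described as the average or established-service effect, and the cost-effectiveness and cost-benefit results are shown under both estimates.

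Do not use a pooled term for month 3 or later as the established-service effect. It is itself biased if the effect continues to change after month 3.

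The cost is a few sentences and one further model on data already held. The drawback is precision: SE 4.7 to 5.5 points against 3.5. For a 10-point effect at two-sided 2.5%, the equal-months average has power of about Φ(0.10/0.055 − 2.241) ≈ 33%, against about 74% for the single term in the same layout (Φ(0.10/0.0346 − 2.241)). The service-time model should therefore guide interpretation and not serve as a second test.

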Virtual pharmacy services have been implemented across parts of rural and remote Australia, particularly Queensland, however much of the literature reports on outpatient medication reviews rather than inpatient services [16, 22–24]. A feasibility study evaluating a service providing virtual clinical pharmacy reviews for inpatients in rural and remote regions was found to be acceptable [23]. Despite this, few studies have since reviewed service efficacy, with most studies focussing on patient satisfaction [23]. The use of virtual service delivery has been demonstrated to increase accessibility to specialist care particularly for rural and remote populations including Aboriginal communities, with evidence supporting the use of virtual technologies for the management of chronic diseases [25].

Three small studies have assessed the feasibility and acceptability of virtual pharmacy services in rural and remote locations [16, 23, 24]. This study will add to existing literature to provide evidence about the feasibility and efficacy of virtual pharmacy services in relation to patient outcomes, patient experience and economic factors.

The VCPS evaluation aims to 1.) Investigate if the VCPS results in a detection of preventable medication harms, reductions of readmission, falls and length of stay; 2.) Identify if the VCPS is cost-effective; and 3.) Assess if the VCPS is perceived to be an acceptable service for patients and clinicians.

Western NSW Local Health District (WNSWLHD) and Far West Local Health District (FWLHD) comprise some of the most remote regions in NSW, Australia. The two districts cover almost 450,000km^2^ with a population of 300,000 people. Services are provided by a combination of rural referral hospitals, rural hospitals, multipurpose facilities and nurse-only remote clinics. Onsite clinical pharmacy services are provided to only seven of thirty eight facilities, resulting in noncompliance with Standard 4 of the National Safety & Quality Health Service Standards (NSQHS) [13]. Existing telehealth infrastructure along with recent roll out of electronic medication management (eMeds) in the electronic medical record (eMR), has provided the infrastructure for a virtual clinical pharmacy service (VCPS).

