Virtual clinical pharmacists will conduct Med Rec on admission, discharge or transfer and document a medication history in eMeds. A summary of the Med Rec and any identified issues will be documented on the eMR Medication Management Plan. To ensure continuity of medication management on discharge back to the community, the pharmacist will provide an updated medication list on discharge. The virtual pharmacist will provide comprehensive information to the patient or carer to enable safe and effective use of the medications. This will be tailored to suit the patient’s individual circumstances and may be in the form of verbal instructions, demonstration, education, a medication list, written advice or a consumer medicines information sheet. Pharmacists will also undertake clinical medication review for inpatients of the facilities and provide medication advice to Doctors and Nurses. Any harms or clinical incidents arising from the VCPS will be addressed using the NSW Health Incident Management System (IMS) and investigations will be conducted according to clinical governance processes.

Routinely collected, de-identified health data will be analysed pre and post VCPS (see Table 1). Data will be collected from the electronic medical record and Health Intelligence Unit (HIU) reports. A waiver of consent has been granted for this de-identified data. Patients receiving the service will be invited by nursing staff at their facility to complete a patient experience measure and a medication non-adherence questionnaire [26]. Staff at participating hospitals will be invited by email from the research team to a focus group about their experience of the virtual pharmacy service. Participation will be voluntary and written consent required.

**Table 1 Tab1:** Measures and routinely collected data source for VCPS evaluation

Outcome Measure	Data Source	Level of Data
% medication reconciliation on admission	eMR Report EM002	Facility
% medication reconciliation on discharge	eMR Report EM002	Facility
VTE Prophylaxis rates	Audit Office report	Facility
Antimicrobial usage	iPharmacy Dispensing Software	Facility
% medication list on discharge	Custom eMR report	Patient
28 day readmission	HIU report	Facility
28 day readmission Aboriginal patients	HIU report	Facility
Length of stay	HIU report	Facility
Length of stay Aboriginal patients	HIU report	Facility
Falls	HIU report	Facility
Detection of preventable medication errors	HIU report	Facility

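### The blanket exclusion of transferred separations also covers falls and detected medication errors, which occur before transfer and may lead to it

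*Protocol article*

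**What the plan says.** All of this is in the protocol article, mostly in Methods/design.

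- **Rule.** After naming the outcomes and the models, the outcomes paragraph states: "Analyses will exclude separations where the patient is transferred to another facility". It gives no reason, and exempts no outcome.
- **Primary outcomes.** The admission outcome is "the proportion of separations (“discharged home by the hospital”) where the medication reconciliation occurred on admission". The discharge outcome has the same denominator, and the Appendix table repeats both definitions.
- **Secondary outcomes.** "Secondary outcome variables include 28-day readmission, hospital length of stay (LOS), number of falls and detection of medication-related errors". None of these carries a discharged-home restriction of its own.
- **Model.** "Our analyses will comprise generalised linear mixed models, with fixed effects for time, period (pre vs post), and patient-level confounding variables", with random terms at hospital and patient level.
- **Population and service.** "All adult patients of emergency departments and inpatient wards of the participating hospitals will be included in the study". The Appendix lists exclusion criteria, and transfer is not among them. On delivery: "Virtual clinical pharmacists will conduct Med Rec on admission, discharge or transfer".
- **Aim.** The Background section sets out to "Investigate if the VCPS results in a detection of preventable medication harms, reductions of readmission, falls and length of stay".
- **Source.** Table 1 takes falls and preventable medication errors from Health Intelligence Unit reports at facility level.

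**The concern.** Whether a separation ends in transfer is known only at its end, after the patient has been exposed to control or VCPS care. A fall or a medication error at the study hospital comes earlier and may be why the patient is moved. For these two outcomes the rule selects on a possible consequence of the outcome itself.

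Two things can follow. Events that led to transfer leave the count. And if the service changes who is transferred, or acts mainly on the harms that lead to transfer, the comparison of control with VCPS months is distorted. Randomising the order of sites and adjusting for calendar time does not repair this, because the selection can itself differ between the two conditions.

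Falls and medication harms are part of the trial's first aim. The cost-benefit analysis also puts a value on treating them, so it would inherit the problem if it takes its effects from these models.

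**Working it through.** **What the documents supply.** They give no transfer rate, no fall rate and no share of falls or errors that end in transfer, so the plan has no figure on this point to reproduce. All rates below are assumptions, used only to show how the rule behaves.

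**Set-up.** Let f be the risk of a fall per separation, q the probability that a patient who falls is transferred, and p the probability that any other patient is transferred. With transfers excluded,

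analysed risk = f(1−q) / [f(1−q) + (1−f)(1−p)].

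**Case 1: transfer works the same way in both periods.** Take q = 0.30 and p = 0.15 throughout, with f falling from 0.03 to 0.024 (true ratio 0.80).
- Control: 0.03 × 0.70 = 0.021; 0.97 × 0.85 = 0.8245; 0.021/0.8455 = 2.48%.
- VCPS: 0.024 × 0.70 = 0.0168; 0.976 × 0.85 = 0.8296; 0.0168/0.8464 = 1.98%.
- Analysed ratio: 0.80. Thirty per cent of falls are lost, but the comparison is essentially intact.

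**Case 2: no true effect, but transfer of fallers changes.** Take f = 0.03 and p = 0.15 in both periods.
- q from 0.30 to 0.20: 0.021/0.8455 = 2.48% against 0.024/0.8485 = 2.83%; ratio 1.14.
- q from 0.40 to 0.20: 0.018/0.8425 = 2.14% against 2.83%; ratio 1.32.
- q from 0.20 to 0.30: 2.83% against 2.48%; ratio 0.88.

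The true ratio is 1.00 each time, and counting all separations would return it.

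**Case 3: the service prevents the falls that lead to transfer.** Split falls into minor (risk m) and severe (risk s). Assume that every severe fall is transferred, that everyone else is transferred with probability p, and that the service halves s and leaves m unchanged. The factor (1−p) cancels, so analysed risk = m/(1−s), and the share of control-period falls counted is m(1−p)/(m+s).
- Falls 4%, half severe: true ratio (0.02 + 0.01)/0.04 = 0.75. Analysed: 0.02/0.98 = 2.04% against 0.02/0.99 = 2.02%; ratio 0.99. Share counted with p = 0.20: 0.02 × 0.80/0.04 = 40%.
- Falls 2%, one in ten severe: true ratio (0.018 + 0.001)/0.02 = 0.95. Analysed: 0.018/0.998 against 0.018/0.999; ratio 1.00. Share counted with p = 0.10: 0.018 × 0.90/0.02 = 81%.

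**Medication errors.** The same formula applies with f as the risk that an error is detected. A working service may raise detection, so the direction found in Case 3 does not carry over.

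**Reading.** Lost events alone do not bias the ratio (Case 1). Bias needs transfer, or its link to the event, to differ between periods (Case 2), or the service to act on the events that lead to transfer (Case 3).

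**The case against.** Much of the opposing case stands, and it limits the point.

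- **Co-primary outcomes.** A reader might infer that the rule costs the admission outcome part of its data. The documents do not support that. Both co-primaries are defined on separations discharged home, so transferred patients are outside the denominator with or without this sentence. The planning figure of 29 separations per site per month may already be net of transfers.
- **Length of stay.** A reader might want transfers put back here too. Transfer cuts the stay at the study hospital short, so counting it as a completed stay would bring in a bias of its own.
- **Direction.** A reader might infer that benefit is pulled toward no effect. That is one assumed scenario; others go the opposite way, and the error outcome concerns detection rather than occurrence.
- **Premise.** No section says that falls or medication harm lead to transfer at these hospitals, or that the service alters transfer. Both are plausible but undocumented.
- **Scope.** The sentence belongs to the routine-data models. The patient experience survey, adherence questionnaire and staff focus groups are specified separately.
- **Service delivery.** Reconciling medicines at transfer describes the service and does not contradict a narrower analysis set.
- **Facility-level counts.** Table 1 leaves open how a separation-level exclusion would be applied to facility reports, so it is not shown that severe falls will in fact be dropped. This does not remove the concern: the stated models use patient-level covariates and a patient random effect, and the rule as written exempts no outcome.

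**Conclusion.** The point holds for falls and detection of medication-related errors in the routine-data analyses. Followed as written, the rule conditions these two secondary outcomes on an event that comes after exposure and may result from the outcome. It also narrows a population that the protocol otherwise defines as all adult patients.

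Size and direction cannot be taken from the documents. The illustrations (analysed ratios of 0.88 to 1.32 under no effect; a true 0.75 to 0.95 analysed as 0.99 to 1.00) rest on assumed fall risks of 2 to 4%, assumed transfer of 10 to 20% among other patients, and assumed links between falls and transfer. They show what the rule can do, not what it will do in this trial.

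The restriction follows from the denominator for discharge reconciliation and can be defended for 28-day readmission. The admission co-primary outcome needs no change of definition. The point deserves correction because it concerns a stated aim and is cheap to put right, but it does not threaten the primary analyses.

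**What to change.** 1. Limit the transfer exclusion to outcomes that require discharge home: discharge reconciliation, and 28-day readmission where that can be justified.
2. Count falls and detected medication-related errors over all eligible adult separations, or per patient-day at the study hospital, whatever the mode of discharge. State how this is done with the facility-level reports.
3. Report transfer rates separately for control and VCPS months, so that readers can judge whether selection could matter.
4. Keep the registered discharged-home definition for the admission co-primary outcome, and add an all-separations version as a sensitivity analysis only.
5. Keep the main length-of-stay analysis on patients discharged home, and add a sensitivity analysis that treats transfer as a competing or censoring event.

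The cost is changed analysis wording (with the matching registry update), a slightly wider data request that includes mode of discharge, and a little more analysis work. Design and patient care are unaffected.
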